### Randomization and study treatment

Eligible patients will be randomly assigned, in a 1:1 ratio, to one of the two treatment arms. Randomization will occur either at ICU admission or when the eligibility criteria are met if the patient was admitted for a reason other than ARF. Randomization will be performed via the website telemedicine cleanweb.aphp. After having completed the randomization webpage, the investigator will receive the treatment arm designation. Time zero will be defined by randomization time. Randomization will be stratified by center, oxygen flow rate at randomization (>or ≤9 L/min), and reason of immunosuppression (oncologic and hematologic malignancy or immunosuppressed treatment and solid organ transplantation). All the data will be notified in an e-CRF on the website telemedecine cleanweb.aphp.

In the early NIV group (intervention group), NIV sessions will be administered throughout the 24-hour cycle, with oxygen therapy sessions in the intervals, the objective being to maintain SpO_2_ > 92%. NIV would be given for at least six out of 24 hours during the first 24 hours. In the oxygen-only group (control group), continuous oxygen therapy will be provided to maintain SpO_2_ > 92%.

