### Statistical analysis

The analysis will be performed according to the intention-to-treat approach. We will use the chi-square test to compare 28-day mortality rates in the group managed with oxygen only and in the group managed with oxygen and early NIV. Randomization will be stratified on the underlying disease (hematological or solid malignancy versus other) and on ARF severity as assessed by the baseline oxygen flow rate (≤9 L /min versus >9 L/min to obtain SpO_2_ > 95% and/or resolution of the signs of respiratory distress). We will test for an interaction between the treatment effect and the underlying disease. If such an interaction is found, we will use the chi-square test to look for a treatment effect within the stratification subgroups. We will correct for the multiple comparisons using the Bonferroni test (error of first order 0.025). Similarly, we will look for an interaction between the treatment effect and baseline ARF severity. If such an interaction is found, we will use the chi-square test to look for a treatment effect within the stratification subgroups. We will correct for the multiple comparisons using the Bonferroni test (error of first order 0.025).

For the secondary evaluation criteria, we will use the chi-square test to compare the proportions of patients with treatment failure (defined by the need of IMV), and nosocomial infection in the two treatment arms. The procedure described above for potential subgroup analyses of the primary evaluation criterion will be used for these secondary evaluation criteria. Wilcoxon’s test will be performed to compare the number of organ failures (SOFA score) between the two arms 72 hours after study inclusion. Median hospital and ICU length of stay will be compared between the two arms using the Kaplan-Meier estimator, with discharge alive as the event of interest and death as the censoring event. Time on invasive mechanical ventilation will be compared between the two arms using the log-rank test.

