### Sample size estimation

Based on previous studies in the field and on evidence of declining mortality rates over the last decade among ICU patients with hematological or solid malignancies
[12, 13, 18, 19], we expect 28-day mortality rates of 20% in the early NIV arm and 35% in the oxygen-only arm. With alpha set at 0.05, 90% power, and the chi-square test, 187 patients are needed in each arm, totalling 374 patients in all. A single interim analysis to assess superiority is scheduled. The interim analysis will take place after inclusion of half the patients (n = 187). The criteria for premature study discontinuation based on the results of this single interim analysis will be those defined by O’Brien and Fleming
[20]. All tests will be two-sided. The statistical analysis will be performed using SAS 9.1.3 (SAS, Inc., Cary, NC, USA) (or a more recent version) or R.2.15.2 (R foundation for statistical computing, Vienna, Austria). (or a more recent version).

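### The 0.025 subgroup level corrects within one factor only, so the chance of some false 28-day mortality claim, overall or in a subgroup, is about 9% to 10%

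*Protocol article*

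**What the plan says.** The Statistical analysis section of the protocol article compares 28-day mortality between arms with one chi-square test. It then sets out a subgroup procedure for two of the randomization stratification factors, each with two levels: underlying disease (malignancy or other) and baseline oxygen flow (up to or above 9 L/min).

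- For underlying disease, an interaction test comes first. If an interaction is found, a chi-square test is run in each of the two subgroups.
- The second factor is handled in the same way: "Similarly, we will look for an interaction between the treatment effect and baseline ARF severity".
- After each factor the section states: "We will correct for the multiple comparisons using the Bonferroni test (error of first order 0.025"). The sentence appears twice, once per factor.
- For need of IMV and nosocomial infection: "The procedure described above for potential subgroup analyses of the primary evaluation criterion will be used for these secondary evaluation criteria".

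The section Sample size estimation gives the overall error level: "With alpha set at 0.05, 90% power, and the chi-square test, 187 patients are needed in each arm". It adds: "All tests will be two-sided". The article gives no significance level for the interaction tests and does not make subgroup testing depend on the overall mortality result.

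**The concern.** The level 0.025 is 0.05 shared between two tests, that is, the two subgroups of one factor. It is used unchanged for the second factor, so mortality alone has four possible subgroup tests at 0.025, besides an overall test that already uses the full 0.05. Since the subgroup step runs whatever the overall test shows, it opens further routes to a mortality claim.

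At stake is how a null trial would be reported. With no overall difference, the written procedure still allows a significant mortality effect to be declared in, say, patients with malignancy or those on low oxygen flow, and described as corrected for multiple comparisons. The correction does not cover the whole set of mortality tests from which such a claim would be drawn.

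**Working it through.** **Inputs.** Two-sided alpha 0.05, 90% power and 187 per arm (Sample size estimation); expected mortality 20% and 35% (same section); 1:1 allocation (Randomization and study treatment); two binary factors and a subgroup level of 0.025 (Statistical analysis). The interaction level is not stated; 0.05 and 0.10 are assumed.

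**1. The plan's own figures.** With pooled proportion 0.275:

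n = [1.960·√(2·0.275·0.725) + 1.282·√(0.35·0.65 + 0.20·0.80)]² / 0.15² = 184.1, so 185 per arm, against 187 stated. The sample size is reproduced to within two patients, and it is for the single overall comparison at 0.05. The subgroup level is 0.05/2 = 0.025 exactly.

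**2. Error under no treatment effect, mortality only.** Take two independent factors with 50/50 splits. The overall statistic Z and the interaction statistics I₁ and I₂ are then approximately independent standard normal variables, and the two subgroup statistics for factor k are (Z + Iₖ)/√2 and (Z − Iₖ)/√2. The larger of these in absolute value is (|Z| + |Iₖ|)/√2. The critical value at two-sided 0.025 is 2.241, so factor k yields a false subgroup claim when both

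- |Iₖ| exceeds 1.960 (interaction level 0.05) or 1.645 (level 0.10), and
- |Z| + |Iₖ| exceeds 2.241·√2 = 3.170.

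Let q(z) be the probability of this for one factor given Z = z. The chance of a claim from either factor is then 1 − (1 − q(z))². Integrating over z gives:

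| Quantity | Interaction level 0.05 | Interaction level 0.10 |
|---|---|---|
| Overall test | 5.0% | 5.0% |
| Subgroup claim, one factor | 2.1% | 3.0% |
| Subgroup claim, either factor | 4.1% | 5.7% |
| Subgroup claim with overall test non-significant | 3.6% | 4.8% |
| Any mortality claim (first row plus fourth) | 8.6% | 9.8% |

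**3. Simulation checks.**

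- Normal scores, 1,000,000 runs: 8.6% and 9.7% with 50/50 splits; 8.9% and 9.8% with splits of 80/20 and 60/40.
- Patient-level data (20,000 trials per scenario, 374 patients, mortality 27.5% in both arms, overall test at the O'Brien-Fleming final critical value of 1.977): overall error 4.7–4.8%, any mortality claim 8.2–8.9% and 9.4–9.9%.

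**4. What the interaction requirement does.** Without it, a false subgroup claim from either factor would occur in about 8.5% of null trials, and any mortality claim in about 10.4%. The requirement therefore cuts subgroup errors to about 4% or 6%. It does little for the combined rate, because most of the false subgroup claims that remain fall in trials with a non-significant overall test (3.6/4.1 and 4.8/5.7, that is, more than four in five).

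**5. Direction.** These rates count benefit and harm. Claims favouring NIV rise from 2.5% (overall test alone) to 4.4% (interaction level 0.05) or 4.9% (level 0.10).

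**6. Power of a subgroup test.** A stratum with half the patients has 93.5 per arm: 0.15/√((0.16 + 0.2275)/93.5) = 2.33 against 2.24, so power is about 53.5% for 20% versus 35%.

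**The case against.** The case for leaving the text alone has real weight.

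- **The only 0.05 belongs to the primary comparison, and that comparison is not inflated.** This stands. The article nowhere promises 5% over all tests together.
- **Within its own scope the correction roughly works.** With an interaction level of 0.05, mortality subgroup errors over both factors are about 4%, below 5%; at 0.10 they are about 6%. This also stands. The excess comes mainly from adding subgroup claims, not conditional on the overall result, to an overall test that already uses 0.05.
- **The analyses are ranked.** There is one primary criterion, the others are called secondary, and nothing says that a subgroup result may establish efficacy. A condensed article may leave labelling to the full protocol. This is fair as far as it goes. Here, though, the article does not merely omit a label: it fixes a numerical testing rule, gives it an error level and says that it corrects for the multiple comparisons.
- **Making subgroup tests wait for overall significance could hide opposite effects in two strata.** This is a good reason not to recommend that route.

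A reader might go further and infer that false efficacy claims far exceed a stated 5%. The documents do not support that. Much higher figures arise only by pooling the secondary endpoints. Mortality plus subgroup claims on all three endpoints gives 14.5–19.8%, and this rests on assumed rates (IMV 40%, infection 20%), strata splits and correlations. Adding the secondary overall tests gives 17–28% (interaction levels up to 0.15), but 10–14% comes from testing three endpoints overall at 0.05, with no subgroup test. All these rates are two-sided and so include false findings of harm.

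**Conclusion.** The point holds in a limited form. The 0.025 level is a within-factor correction that takes no account of the second factor or of the overall mortality test, and subgroup testing is not tied to that test. The primary test keeps its 5% error. Under no treatment effect, the chance of some mortality claim, overall or in a subgroup, is about 9% (interaction level 0.05) or 10% (level 0.10). About 4 to 5 percentage points of this arise in a subgroup after a non-significant overall result. Carrying the rule over to need of IMV and nosocomial infection adds further uncorrected tests.

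The figures rest on the assumed interaction level, independent factors and the strata splits shown, and the chance of stopping at the interim analysis is not modelled. They change little across the splits tried. The main comparison and the sample size are unaffected, so this is a worthwhile correction and not a threat to the trial's primary conclusion.

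**What to change.** In the Statistical analysis section:

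1. State that the overall 28-day mortality comparison is the only confirmatory test.
2. Replace the within-subgroup chi-square tests at 0.025 with exploratory estimates: the treatment effect in each stratum with its 95% confidence interval, plus the interaction p-value. Report them whatever the interaction test shows, and without significance claims.
3. Do the same for need of IMV and nosocomial infection.
4. Remove the statement that 0.025 corrects for the multiple comparisons.

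Tightening the subgroup level alone would not be enough: at 0.0125 (0.05/4), with the overall test still at 0.05, the chance of any false mortality claim falls only from 8.6% to 7.0%, or from 9.7% to 7.3% with an interaction level of 0.10.

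The change is to wording only and needs no new data or patients. The sponsor gives up a formal subgroup claim, for which the trial was not sized.

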## Methods/Design

The IVNIctus trial is a prospective, multicenter, open-label, randomized controlled trial comparing a management strategy including early NIV with oxygen alone in immunocompromised patients admitted to ICU with ARF. Early NIV is defined as NIV treatment for patients with ARF who are without any other organ failure or intubation criteria (intubation criteria would be described further (in patient management bias paragrah)).

The study hypothesis is that early NIV decreases mortality in immunocompromised patients requiring ICU admission for ARF. The primary evaluation criterion is survival on day 28 after randomization. Secondary evaluation criteria are proportion of patients treated with IMV in each group, number of organ failures (Sequential Organ Failure Assessment score) 72 hours after randomization in each group, invasive mechanical ventilation duration and ICU stay length in each group, patient comfort in each group, frequency of nosocomial infections in each group, survival at six months after randomization.

The primary study objective is to demonstrate that in immunocompromised patients admitted to the ICU with ARF, a management strategy including early NIV improves 28-day mortality compared to high-flow oxygen without NIV.

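### Kaplan-Meier medians with death censored do not describe time to live discharge among all randomised patients, and the error is larger in the arm with more deaths

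*Protocol article*

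**What the plan says.** In the protocol article, Statistical analysis, the plan for length of stay is a single sentence: "Median hospital and ICU length of stay will be compared between the two arms", by the "Kaplan-Meier estimator, with discharge alive as the event of interest and death as the censoring event". This fixes the estimator, the event and the handling of deaths. Nothing else in the article deals with deaths in the analysis of stay.

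ICU stay is a named secondary criterion in Methods/Design ("invasive mechanical ventilation duration and ICU stay length in each group"). Hospital stay is not in that list. It appears among the end-of-participation evaluations and in the analysis sentence.

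Deaths are expected to be frequent and unequal. Sample size estimation states: "we expect 28-day mortality rates of 20% in the early NIV arm and 35% in the oxygen-only arm". Methods/Design makes the difference the aim of the trial: "The study hypothesis is that early NIV decreases mortality in immunocompromised patients requiring ICU admission for ARF".

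**The concern.** Kaplan-Meier treats a censored patient as someone who could still have the event later, at the rate seen in those still at risk. That is reasonable for a patient lost to follow-up but not for one who has died. Censoring deaths passes the probability of the dead on to later live discharges. The resulting curve describes a setting in which nobody dies in the unit, and even that reading needs death and discharge to be independent given what is modelled.

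The median from such a curve is not the time by which half of the randomised patients have left alive. It comes too early, and the gap grows with mortality. If the trial's own hypothesis is true, the two arms are therefore distorted by different amounts. The reported comparison could show equal stays where half the patients have left alive days earlier in one arm than in the other.

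**Working it through.** **Are the mortality inputs coherent?** The article gives no figure for stay, so the figure to reproduce is the sample size: "With alpha set at 0.05, 90% power, and the chi-square test, 187 patients are needed in each arm, totalling 374 patients in all". Tests are two-sided and allocation is 1:1. With pooled variance and no continuity correction:

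n = [1.960·√(2·0.275·0.725) + 1.2816·√(0.35·0.65 + 0.20·0.80)]² / 0.15² = (1.2377 + 0.7978)² / 0.0225 ≈ 184.1, so 185 per arm.

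This is within 2 per arm of the stated 187, and power at 187 is 90.4%. The 20% and 35% can be used as the plan's own mortality inputs.

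**Assumptions for stay.** These are not in the document:
- The hazard of live discharge, d, is constant and the same in both arms, and is varied from 0.05 to 0.15 per day.
- The hazard of death before discharge, h, is constant. It is solved in each arm so that deaths by day 28 equal 20% (NIV) or 35% (oxygen): h/(d+h) · [1 − exp(−28(d+h))] = 0.20 or 0.35.

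**Formulas.**
- Kaplan-Meier median with death censored: ln 2 / d. It does not depend on h.
- Cumulative-incidence median (half of all randomised patients discharged alive): −ln(1 − 0.5/s) / (d+h), with s = d/(d+h).

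**One case in full, d = 0.08.**
- Both arms, Kaplan-Meier: 0.6931/0.08 = 8.66 days.
- NIV: h = 0.0216, d+h = 0.1016, s = 0.787. Median = −ln(1 − 0.635)/0.1016 = 9.92 days.
- Oxygen: h = 0.0452, d+h = 0.1252, s = 0.639. Median = −ln(1 − 0.7825)/0.1252 = 12.18 days.

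**Range** (days; errors taken before rounding):

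| d per day | h NIV / oxygen | KM median, both arms | Cumulative-incidence median, NIV | Cumulative-incidence median, oxygen | KM too short by, NIV / oxygen |
|---|---|---|---|---|---|
| 0.05 | 0.0156 / 0.0319 | 13.86 | 16.27 | 20.86 | 2.41 / 7.00 |
| 0.08 | 0.0216 / 0.0452 | 8.66 | 9.92 | 12.18 | 1.25 / 3.52 |
| 0.10 | 0.0260 / 0.0549 | 6.93 | 7.89 | 9.62 | 0.96 / 2.69 |
| 0.15 | 0.0377 / 0.0810 | 4.62 | 5.24 | 6.36 | 0.61 / 1.74 |

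The error in the oxygen arm is about 2.8 to 2.9 times that in the NIV arm throughout. Kaplan-Meier shows no difference where the cumulative-incidence medians differ by 1.1 days (6.36 − 5.24) to 4.6 days (20.86 − 16.27).

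**Consistency check at day 28, d = 0.08.** One minus Kaplan-Meier is 1 − exp(−2.24) = 89% in both arms. In the oxygen arm, 89% discharged alive plus 35% dead makes 124%, which is impossible as a description of the randomised patients. The cumulative incidences are 62% (oxygen) and 74% (NIV).

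**Simulation at d = 0.08, 187 per arm.** Kaplan-Meier medians were 8.7 and 8.7 days, and cumulative-incidence medians 9.9 (NIV) and 12.3 (oxygen), in agreement with the formulas.

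**The case against.** Four arguments limit the point.

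**Too short for what?** A reader might infer that the planned medians understate length of stay in every sense. They do not. If stay means time in the unit until exit by any route, they are too long. At d = 0.08 the median time to any exit is ln 2/0.1016 = 6.8 days (NIV) and ln 2/0.1252 = 5.5 days (oxygen), both below the Kaplan-Meier 8.7. The direction holds only for time to live discharge counted over all randomised patients. The article does not say which quantity it wants. This objection stands, and the point is limited accordingly.

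**Is the comparison itself invalid?** A reader might also infer that no valid test is available under death-censoring. That is not supported. An article may leave the test to the analysis plan, and a log-rank test with deaths censored is a valid comparison of cause-specific hazards of live discharge. The fault is confined to presenting Kaplan-Meier medians as stay.

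**Is a null result wrong if NIV changes only death?** Not as a cause-specific answer: the discharge rate among those still in the unit is indeed unchanged. Conversely, under a cumulative-incidence or subdistribution analysis alone, a pure mortality effect looks like faster discharge. This stands, and it is why the remedy needs both views.

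**How firm are the days?** They depend on discharge rates that the article does not give, and on counting the planned 28-day deaths as deaths before discharge. If some occur after ICU discharge, the error for ICU stay is smaller. With equal mortality and equal discharge hazards, both medians would still be too short for live discharge, but by the same amount.

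**Conclusion.** The point holds in this limited form. The plan explicitly fixes an estimator whose medians do not describe time to live discharge among all randomised patients. For that quantity they are too short by 0.6 to 2.4 days with NIV and 1.7 to 7.0 days with oxygen. This rests on constant hazards, the same live-discharge hazard of 0.05 to 0.15 per day in both arms, and 20% and 35% dead before discharge by day 28. The sizes in days are illustrative. The direction, and the larger error in the arm with more deaths, do not change over that range.

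A reader might take this as a threat to the trial's main conclusion. The documents do not support that: ICU stay is one of several secondary criteria, and the chi-square comparison of 28-day mortality, the sample size and the interim rule do not depend on it. It is a clear error in a secondary analysis, to be corrected before the data are analysed.

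**What to change.** In Statistical analysis, replace the Kaplan-Meier sentence with text to this effect: the cumulative incidence of discharge alive, from the ICU and separately from hospital, will be estimated in all randomised patients with death before discharge as a competing event (Aalen-Johansen estimator). Arms will be compared by Gray's test or a subdistribution hazard model. The median time to live discharge will be read from the cumulative incidence curve, and reported as not reached where fewer than half are discharged alive. Cause-specific hazards of live discharge and of death will be reported alongside, so that a pure mortality effect is not read as faster discharge.

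The sentence should also state the quantity of interest: time to live discharge counting deaths as never discharged, rather than time in the unit until any exit.

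The cost is the rewording of one sentence. Lengths of stay and mortality are already to be recorded, and the named software (SAS or R) has routines for these methods. Sample size and primary analysis stay as they are.

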### Sample size estimation

Based on previous studies in the field and on evidence of declining mortality rates over the last decade among ICU patients with hematological or solid malignancies
[12, 13, 18, 19], we expect 28-day mortality rates of 20% in the early NIV arm and 35% in the oxygen-only arm. With alpha set at 0.05, 90% power, and the chi-square test, 187 patients are needed in each arm, totalling 374 patients in all. A single interim analysis to assess superiority is scheduled. The interim analysis will take place after inclusion of half the patients (n = 187). The criteria for premature study discontinuation based on the results of this single interim analysis will be those defined by O’Brien and Fleming
[20]. All tests will be two-sided. The statistical analysis will be performed using SAS 9.1.3 (SAS, Inc., Cary, NC, USA) (or a more recent version) or R.2.15.2 (R foundation for statistical computing, Vienna, Austria). (or a more recent version).

### Provisional time table

Based on the recruitment rates in the TRIAL-OH study
[21] of consecutive hematology patients admitted to the same ICUs (appendix 4, study ongoing), the 30% proportion of patients with ARF who were not intubated at ICU admission in the same study, and the admission rate of immunocompromised patients in the study centers, recruitment is expected to last approximately 30 months. The Data and Safety Monitoring Committee will meet regularly to review adverse events recorded during the trial. The overall data analysis will be performed under the responsibility of [name] and [name] at the Biostatistics Department of the Saint-Louis Teaching Hospital, Paris, France.

